### Trial procedures

General practices were approached by letter inviting them to take part in the trial. Once a practice had consented, potential participants for telehealth were identified in each site using existing registers of patients with long-term conditions in general practice. Potential participants for telecare in each practice were identified from databases held by social services departments.

To meet ethical obligations, patients were asked to complete and return a 'data sharing letter' if they consented to their data being shared with the research team. Once this letter was received, patients received a 'light touch' visit from a member of the project team in each site, where consent was taken to (a) participate in the main trial (Theme 1) and (b) the questionnaire study (Themes 2 and 3).

Participants who agreed to take part in the Themes 2 and 3 were subsequently contacted by a market research company to arrange a convenient time for the baseline interview. At this interview, patients received information about this part of the study and signed consent. The baseline assessment varied by participant status (i.e. COPD, heart failure, diabetes, telecare, carers) but each comprised a core of standardised PROMs. The PROMs were self-completed by the participant with the researcher on hand to explain or clarify. Data on health care utilisation were collected via interview. The average total time for assisted baseline interview completion was 80 minutes.

Carers of service users in the trial were identified by sites usually at the 'light touch' visit, either by the carer expressing an interest or via *snowball sampling *(i.e. asking participants if they had an informal carer at the baseline interview).

Each practice was allocated to groups via a centrally administered minimisation algorithm. The allocation determined the technologies available to each practice (i.e. either telehealth or telecare) and their associated patients. Following installation of the technologies, participants will be followed-up for 12-months. After 12-months, the 'usual care' groups were eligible to receive the appropriate interventions.

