Data on health, social care and other support service use for participants will be collected using the CSRI [30]. Unit costs will be attached to service use data to calculate a total cost per patient at baseline, 3 months and 12 month follow up. Costs will be calculated on the basis of the costs incurred in the 3 months prior to the 3 data collection points. Service use and associated costs for participants in both trial arms will be reported under sub-categories such as use of acute hospital services and community social services. All cost categories will be allocated to a perspective (whether NHS, Local authority, NHS and Local authority, or public sector). The costs of the intervention will be calculated specifically for this study from data provided by the sites and those costs attached to participants receiving the intervention in the telehealth and telecare groups. Point estimates of the costs for the control and intervention groups in each trial arm will be derived from univariate and multivariate analyses of costs from all 4 perspectives.

The effectiveness of the telehealth and telecare programmes will be compared using a common unit of outcome measurement, the QALY, to be constructed from the EQ-5D health state classification [16] scored using established algorithms (York Tariff) [41]. QALY scores will be calculated for the baseline, 3 month and 12 month follow-up points. In addition, scores from a broader measure of quality of life intended for health and social care evaluations, the ICECAP [14], will be examined. ICECAP scores at each time point will be presented for all three time points. Incremental cost effectiveness ratios (ICER) will be calculated at the 3 month and 12 month follow up points for both trial arms. The ICER will be defined as the difference in mean costs incurred by the treatment groups in each arm over the previous 3 month period, divided by the difference in mean QALY gain between those treatment groups. A cost-effectiveness acceptability curve (CEAC) will be produced, based on the results of a model of net monetary benefit for clustered data. The CEAC allows the decision-maker to see what is the likelihood of telehealth and telecare being cost-effective at different monetary values of increments of improvement in the chosen outcome.

#### (b) Theme 2

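### The 3-month cost window in the ICER makes no provision for one-off equipment and installation costs; read literally, the 12-month ICER leaves them out

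*Protocol article*

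**What the plan says.** All the relevant text but one sentence is in the protocol article, Analysis, under Themes 1 and 3.

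- Service-use costing: "Unit costs will be attached to service use data to calculate a total cost per patient at baseline, 3 months and 12 month follow up". The next sentence sets the window: "Costs will be calculated on the basis of the costs incurred in the 3 months prior to the 3 data collection points".
- Intervention cost has a separate sentence: "The costs of the intervention will be calculated specifically for this study from data provided by the sites", with "those costs attached to participants receiving the intervention in the telehealth and telecare groups". It gives no timing rule and does not separate one-off from recurrent cost.
- ICER time points: "Incremental cost effectiveness ratios (ICER) will be calculated at the 3 month and 12 month follow up points for both trial arms".
- ICER numerator: "difference in mean costs incurred by the treatment groups in each arm over the previous 3 month period". Denominator: "divided by the difference in mean QALY gain between those treatment groups". The period over which the QALY gain accrues is not given.

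Under Trial procedures, the follow-up clock is tied to installation: "Following installation of the technologies, participants will be followed-up for 12-months".

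**The concern.** The ICER definition comes after intervention costs have been attached to participants, and it makes no exception for them. Intervention cost has to be in the numerator, or the ratio would leave out the technology being evaluated. So the 3-month window applies to it.

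That window suits costs that recur evenly. It does not suit hardware and installation, which arise once at the start. The section on telehealth and telecare describes base units or set-top boxes with several peripherals, so the one-off element may be substantial.

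The technology's own cost is the one cost difference that the design itself creates between the groups. If the 12-month ICER misses the one-off part, the ICER and any acceptability curve built on the same costs lean towards the technology. If the 3-month ICER carries all of it, the lean is the other way. The two time points could then disagree through accounting alone. Scaling does not help: four times the months 9-12 cost still contains no one-off cost, and four times the months 0-3 cost contains it four times.

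**Working it through.** The plan states no equipment price, installation cost, useful life, discount rate or ICER, so there is no figure to reproduce.

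**Step 1: where a one-off cost C falls.** The ICER windows are months 0-3 and months 9-12. Installation is at about month 0.

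- Counted when incurred: up to 100% of C in months 0-3, and 0% in months 9-12. If installation is treated as coming just before follow-up starts, C enters neither ICER. The 12-month result is 0% either way.
- Annuitised over L years at rate r: the share of C per 3-month window is [r/(1-(1+r)^-L)]/4, or 1/(4L) when r = 0. L and r are assumptions.

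| L (years) | r = 0 | r = 3.5% |
|---|---|---|
| 1 | 25.0% | 25.9% |
| 3 | 8.3% | 8.9% |
| 5 | 5.0% | 5.5% |
| 10 | 2.5% | 3.0% |

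On this basis both windows get the same non-zero share.

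**Step 2: does annuitising settle the 12-month ICER?** Only in part. With a level charge, months 9-12 hold 3/12 = 25% of the year's technology charge. If the 12-month QALY gain covers the year, three quarters of the charge is missing. If the gain covers only the last quarter, the periods match.

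**Step 3: illustrative size of literal counting.** Assumptions, none from the documents: outright purchase, one-off cost C of 500 or 1,500 pounds, running cost m of 30 or 60 pounds a month, and a 5-year straight-line life. All four combinations are shown, with C placed inside the first window.

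- Months 0-3, literal: C + 3m
- Months 9-12, literal: 3m
- Quarterly annuitised charge: (C/5 + 12m)/4
- First-year spend: C + 12m

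| C / m | Months 0-3 | Months 9-12 | Quarterly charge | First-year spend |
|---|---|---|---|---|
| 500 / 30 | 590 | 90 | 115 | 860 |
| 500 / 60 | 680 | 180 | 205 | 1,220 |
| 1,500 / 30 | 1,590 | 90 | 165 | 1,860 |
| 1,500 / 60 | 1,680 | 180 | 255 | 2,220 |

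Ratios, in the same order:

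- 3-month cost over quarterly charge: 590/115 = 5.1; 680/205 = 3.3; 1,590/165 = 9.6; 1,680/255 = 6.6.
- 12-month cost over quarterly charge: 90/115 = 0.78; 180/205 = 0.88; 90/165 = 0.55; 180/255 = 0.71. That is 22%, 12%, 45% and 29% too low.
- Months 9-12 as a share of first-year spend: 10.5%, 14.8%, 4.8% and 8.1%.

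The direction is the same in every combination.

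**The case against.** The strongest reply is that the plan never says equipment is expensed when paid. The window sentence follows directly on service-use costing, and intervention cost has its own sentence with its timing left open. An annuitised charge arises in every quarter and fits the ICER definition. Under Interventions and comparisons the article says only that each site has its own supplier agreements, so rental or a managed service is possible, and most of the Step 3 distortion would then disappear. Useful life and annuitisation are details that an article commonly leaves to a fuller economic plan, which is not shown.

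Much of this stands. A reader might infer that the plan definitely puts the whole one-off cost in the 3-month ICER and none in the 12-month ICER, and that both are therefore wrong. The documents do not support that. The split needs a lump-sum purchase counted when incurred, and even then installation may fall on or before the edge of the first window. The prices and asset life in Step 3 are also assumed.

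The reply does not remove the point. The absence of an annuitisation rule is not itself the complaint. The complaint is that the article fixes a numerator of costs incurred in the previous 3 months, applies it at both time points, and does not except intervention cost. Annuitising leaves the 12-month numerator with one quarter's charge, which is right only if the QALY gain also covers one quarter.

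**Conclusion.** The point holds in a conditional form. As written, the ICER rule does not secure a correct technology cost at 12 months.

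- Costs counted when incurred: one-off costs are absent from the 12-month ICER and may fall in full in the 3-month ICER. Under the assumptions in Step 3, the technology cost is 3.3-9.6 times too high at 3 months and 12-45% too low at 12 months relative to a quarterly annuitised charge. Months 9-12 hold about 5-15% of first-year technology spend.
- Costs annuitised or rented, 12-month QALY gain: the 12-month ICER counts 25% of the year's technology charge.
- Costs annuitised or rented, QALY gain over the last quarter only: technology cost and QALY periods agree.

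Only the last case is sound, and the article does not say that it applies. The effect on the ICER itself cannot be computed, because the documents give neither the total cost difference nor the QALY difference. The Theme 1 primary outcome, the proportion admitted to hospital, is unaffected. The point is worth correcting because cost-effectiveness is part of the trial's stated aim, but it is not a must-fix.

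**What to change.** In Analysis, Themes 1 and 3:

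1. Exempt intervention cost from the previous-3-months rule in the ICER definition.
2. Convert equipment, installation and set-up to an equivalent annual cost over a stated useful life. Where a site rents or has a service contract, use the contract charge.
3. State the QALY accrual period at each time point, and charge the annuitised and running costs over that same period.
4. Report full first-year expensing of one-off costs as a sensitivity analysis.

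This takes about one paragraph and a useful-life assumption. The sites already supply the intervention cost data, so nothing more is needed from participants. The downside is that the 12-month ICER may become less favourable to the technology.

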### Outcomes

Theme 1 will collect and link large, administrative datasets with the aim of tracking service use for (a) up to three years pre-intervention and (b) 12 months post- intervention. It will include an assessment of hospital utilisation, including emergency and elective inpatient admissions, inpatient bed day use, outpatient attendances and accident and emergency visits; primary care utilisation, including GP encounters, prescription drugs and community matron visits; and, if possible, social care utilisation such as the use of domiciliary and residential care. Costs will be attributed to activity using national Payment by Results tariffs and reference costs.

Theme 2 and 3 include a comprehensive assessment of PROMs and health utilisation measures at 3 and 12 months, including general quality of life [14-16], disease-specific quality of life (teleheath only) [17-19], psychological well being [20,21], perceived acceptability of telemonitoring devices; use of telehealth and telecare; attitudes, self-efficacy and self-care behaviours [22-25], clinical outcomes (for telehealth participants), social networks [26], illness burden [27], disability [28,29] and health care and social services utilisation [30,31]. Carer outcomes include carer anxiety and caregiver strain [32,33], and carer costs include carer time spent in providing care to the participant as well as lost productivity. The full range of assessment instruments is provided online (Additional file 1).

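### The 12-month ICER takes costs from months 9-12 only, against a QALY gain whose period is undefined; if that gain covers 12 months, the ratio is understated fourfold under a constant cost difference

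*Protocol article*

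**What the plan says.** All of the following is in the Protocol article; the first four items are from Analysis, (a) Themes 1 and 3.

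- Self-reported service costs: "Costs will be calculated on the basis of the costs incurred in the 3 months prior to the 3 data collection points". The collection points are baseline, 3 months and 12 months.
- Outcome: "QALY scores will be calculated for the baseline, 3 month and 12 month follow-up points", constructed from the EQ-5D.
- Ratio: "Incremental cost effectiveness ratios (ICER) will be calculated at the 3 month and 12 month follow up points for both trial arms". The numerator is "the difference in mean costs incurred by the treatment groups in each arm over the previous 3 month period". The denominator is the between-group difference in mean QALY gain.
- Intervention cost: "The costs of the intervention will be calculated specifically for this study from data provided by the sites". The article does not say over what period this cost is spread.
- Trial procedures: "Following installation of the technologies, participants will be followed-up for 12-months".
- Outcomes, Theme 1: the administrative data aim at "tracking service use for (a) up to three years pre-intervention and (b) 12 months post- intervention".

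The article does not state the period over which the QALY gain accrues. It describes no annualising, interpolating or extrapolating of the 3-month costs.

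**The concern.** An ICER has a meaning only if costs and effects accrue over the same period. The same 3-month cost window is prescribed for both ICERs. That suits the 3-month ratio. At 12 months it takes the last quarter of the year and sets it against a gain that most readers would take to be the gain over the whole year.

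Service costs in months 3-9, half of the follow-up, then count in neither ratio. Costs in months 0-3, when equipment is installed and services start up, count only in the 3-month ratio unless they are spread forward.

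Cost-effectiveness is part of the trial's stated research aim (Methods/Design). A 12-month ratio that is wrong by a multiple could change the conclusion drawn from it. Because the article spells out the definition, an analyst who follows it would compute this ratio; the problem is a stated rule and not a missing detail.

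**Working it through.** The article gives no ICER, cost difference or QALY difference, so there is no figure of its own to reproduce. The check compares the periods.

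**Inputs from the article.** Cost windows: the 3 months before baseline, months 0-3 and months 9-12. EQ-5D at 0, 3 and 12 months. ICERs at 3 and 12 months. Month 0 is taken as both baseline and installation.

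**Illustrative assumptions, not from the article.** Cost difference of 100 pounds per month; utility difference of 0 at baseline and 0.03 at 3 and 12 months.

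**Step 1: QALY gain over 12 months, by the trapezium rule.**
0.25 × (0 + 0.03)/2 + 0.75 × (0.03 + 0.03)/2 = 0.00375 + 0.0225 = 0.02625.

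**Step 2: the 12-month ICER under three readings of the QALY gain.** The matched 12-month ICER is 1,200/0.02625 = 45,714 per QALY.

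- Gain over the 12 months (the natural reading): 300/0.02625 = 11,429. Understated by 45,714/11,429 = 4.0.
- Plain difference in 12-month scores: 300/0.03 = 10,000. Understated by 45,714/10,000 = 4.57. Over the four utility paths tried (differences at 3 and 12 months of 0.03 and 0.03; 0 and 0.03; 0.03 and 0.06; 0.06 and 0.03) the factor runs from 2.9 to 10.7.
- Gain in months 9-12 only: 0.25 × 0.03 = 0.0075, so 300/0.0075 = 40,000. The periods match, but this needs a 9-month utility, which is not collected, and it describes only the last quarter.

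**Step 3: how the factor depends on the timing of costs (12-month QALY gain).** The QALY term cancels, so matched ICER / ICER as written = cost difference over months 0-12 / cost difference over months 9-12.

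- Constant at 100 per month: 1,200/300 = 4.0.
- First 3 months at twice the later rate: 1,500/300 = 5.0.
- First 3 months at three times the later rate: 1,800/300 = 6.0.
- Last 3 months at twice the earlier rate: 1,500/600 = 2.5.
- Last 3 months at four times the earlier rate: 2,100/1,200 = 1.75.
- +100 for nine months, then -100 for three: 600/(-300) = -2.0, so the sign is wrong.

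If the technology saves money at a constant rate, the saving is understated fourfold in the same way.

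**Step 4: what this could do to a decision.** At an assumed 20,000 per QALY, the gain of 0.02625 is worth 525. Subtracting the months 9-12 cost gives 525 - 300 = +225; subtracting the 12-month cost gives 525 - 1,200 = -675. This reversal carries over to the acceptability curve only if the net-benefit model uses the same 3-month cost, which the article does not state.

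**Step 5: the 3-month ICER.** The cost window is months 0-3. If the gain is the area over months 0-3, the periods match.

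**The case against.** The strongest reply is that the article never says the QALY gain runs from baseline to 12 months. This stands: it is an inference. A gain limited to months 9-12 is not excluded and would match the costs. However, the assessment times do not support it without an unmentioned interpolation at 9 months, and the result would not be a cost per QALY over the trial's year.

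Other parts of the reply also stand, and they rule out stronger readings that a reader might infer:

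- That the error is fourfold or more. Four is not a lower bound: late-arising costs give 1.75 to 2.5 in the cases tried. The article has no cost data with which to choose among the cases.
- That equipment cost drops out of the 12-month ratio. Intervention cost is calculated separately and attached to participants; how it is spread over time is not stated and may be left to a fuller plan.
- That utilities will be used as if they were QALYs. Speaking of QALY scores at time points is loose, but it does not show that an area under the curve will not be used.
- That the acceptability curve has the same fault. The cost window of the net-benefit model is not given.
- That neither ICER covers a single horizon. The 3-month one can.

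What the reply does not remove is the explicit rule that the 12-month numerator is a 3-month cost, with no step to bring it to a year.

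**Conclusion.** The concern holds for the 12-month ICER. Its cost numerator is fixed at months 9-12, its QALY period is left open, and costs in months 3-9 enter neither ratio. If the gain is the 12-month gain, the ratio is understated exactly fourfold when the cost difference is constant. In the cases tried, it is understated 5 to 6 times with front-loaded costs and 1.75 to 2.5 times with back-loaded costs, and it has the wrong sign if the difference reverses in the last quarter. These sizes rest on assumed cost paths and on the natural, but unstated, reading of the QALY period. The 3-month ICER is sound if its QALY gain is the 0-3 month area. The definition should be corrected before the economic analysis is run, because following it as written can change the cost-effectiveness conclusion.

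**What to change.** Redefine the 12-month ICER over one common 12-month horizon.

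- **QALYs:** area under the EQ-5D curve through baseline, 3 and 12 months.
- **Costs:** 12-month costs. Use the Theme 1 linked data for hospital and other services where available. For services not linked, use a stated interpolation between the self-reported costs for months 0-3 and 9-12, with a sensitivity analysis on that interpolation. Add 12 months of intervention cost, and say how equipment is spread over time.
- **Net monetary benefit and acceptability curve:** use these same cost and QALY quantities.
- **3-month ICER, if kept:** pair months 0-3 costs with months 0-3 QALYs.

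This costs a change of wording and some extra analysis, with no new data collection. There are two downsides. The interpolation covers half the year for any service without linked data; social care is the likely case, since Theme 1 will collect it only where feasible. Mixing sources also brings in differences between administrative and self-reported use, which the article's Discussion says are typically significant, especially in older people and heavy users. Both should be stated alongside the results.

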## Discussion

The proposed study is an ambitious project that is designed to provide a pragmatic yet rigorous assessment of the benefits of (a) telehealth in the management of patients with long-term health conditions, and (b) telecare in the management of patients with social care needs. Figure 7 shows the CONSORT diagram for the recruitment to the trial which shows that 97% of the patient sample size target has been achieved.

**Figure 7 F7:**
[figure not shown]
**CONSORT diagrams (baseline data only)**.

### Advantages and disadvantages of the proposed design

Adoption of the cluster design means that individual patients are not randomised to technology or usual care. This overcomes concerns raised by the participating sites, who felt that individual randomisation was unlikely to be acceptable to patients or professionals: in the adopted design, all general practices will have immediate access to the roll-out of telemonitoring equipment for at least some of their patients. The design thus overcomes concerns about resentful demoralisation among practices [42] if some practices had been randomised to usual care for all their patients, especially as all participants are assessed for the technology after 12 months. The current study is a cluster randomised design, using general practices as the unit of randomisation. However, the present design is an 'individual cluster' design [43]. This means that a cluster randomised design has been adopted for various reasons, but the intervention is still delivered to individual patients. This is unlike a 'cluster cluster' design, where patients in the cluster cannot refuse the intervention (e.g. a water fluoridation trial).

Clearly, the planned analysis by type of technology (telehealth and telecare) ignores differences within technologies. The study has not been powered to explore the effects of individual technologies, but combining different technologies into the primary analysis will lead to debates about their comparability [44]. The qualitative data from Theme 4 may be a useful source of data on variation among users and professionals in their experience of different technologies.

It is important to note that all practices taking part in the evaluation are part of the Whole System Demonstrator pilots, and thus all practices and patients are potentially benefiting from the wider service redesign that is ongoing in these sites. Therefore, the study is assessing the added value of telehealth and telecare technologies over and above the effects of this wider service redesign, and not the benefits of whole systems redesign versus conventional care (see Figure 1). There will therefore be issues concerning the generalisability of the results, because the sites which are part of the Whole System Demonstrator pilots have been specifically chosen for their innovations in these areas of care.

The themes address related issues using a range of methods. For example, Theme 1 exploits large, existing sources of administrative data on service use while Theme 3 collects self-reported data from patients. Several studies have compared health care utilization as described in administrative and self-reported data [45,46]. These have typically found significant differences, especially for people with high levels of use, older people, and for people with poor health status. The trial is also novel in the ways that it exploits data linkage across a range of operational data sets. The advantages of this approach are that it allows the team to access large volumes of computerised data relatively cheaply. This enables analyses of much larger groups but also includes historical data which can be used for risk adjustment and sub-group analyses. The disadvantages are that the data in administrative systems may be of poor quality and it may not capture the most important variables. The combination of administrative data (Theme 1), and directly recorded patient events (Theme 3) provide an opportunity to test whether data problems create different results.

The potential of telehealth and telecare technology to improve care and reduce costs is limited by a lack of rigorous evidence of actual impact. If telehealth and telecare technology proves cost-effective in our trial, it will provide additional options for health services worldwide to deliver care for populations with high levels of need.

